### Intervention

The intervention will be a comprehensive education and restraint distribution program, to be delivered in pre-school settings under the Kids and Traffic program. The Kids and Traffic program offers a road safety orientated education service to all child care services in NSW. Funded by the Roads and Traffic Authority (RTA) of NSW, the 3200 licensed early childhood services registered with the program are sent road safety information, programming advice, posters and information to share with families at least once each year. It has developed a range of strategies, based on the principles of early childhood learning and best practice in early childhood education which support road safety education in pre-school/daycare settings. These include professional development workshops primarily for staff and others designed for both staff and families. The program will be enhanced as part of this trial such that specific material will be developed around increasing use of appropriate child restraints and decreasing incorrect use of child restraints. In line with interventions tested in smaller trials in other settings [25,30], this material will include an educational component (including staff and parent workshops), and will be further enhanced by distribution of child restraints at reduced cost and ongoing distribution and reinforcement of educational materials at the centre level.

The program to be tested in the trial includes the following components:

1. Centres will receive the enhanced workshop from the Kids and Traffic program, with the focus on restraint use. This will require in-service training for staff, and resources for incorporating messages about appropriate restraint use into programming for the centre. Centre staff will also receive monthly policy support from the Kids and Traffic Program staff, and will be provided with extra printed information that can be incorporated into parent newsletters to reinforce messages.

2. Educational material will be provided to intervention centres, consisting of pamphlets and posters about optimal child restraint practices, and information about frequently asked questions, with photographs of appropriate use and incorrect use. Written material will be translated into a range of community languages. These materials will contain specific information about what types of restraints should be used by children in the target age group, and common forms of incorrect use and the impact these have on crash safety. Centres will be asked to display restraint information provided in prominent positions. Approximately 6 weeks following the staff inservice, a parent information session will be held at each centre. This session will include a presentation by the Kids and Traffic personnel, and will include viewing of a DVD created for the trial detailing the benefits of appropriate and correct restraint use and reinforcing recommendations for correct and appropriate use provided in print material, as well as hands-on demonstrations of child restraints. All parents enrolled at each intervention centre will receive material on restraints including the DVD, brochures on appropriate restraints, and written and pictorial information on restraint use. All families will be given a free voucher for a visit to an authorised child restraint fitting station for personalised advice on correct restraint use and will receive information on location of fitting stations in their area.

3. Subsidised child restraints will be made available at a minimal cost ($AUD50, approximately 25% of recommended retail price) for those who require them.

The control group will be offered the standard Kids and Traffic program rather than the enhanced program described above. The current program offers minimal information about use of child restraints so, even if implemented, it is unlikely to have a significant impact on appropriate and correct restraint use. Control sites will be given the option of receiving the enhanced Kids in Traffic workshop at the end of the trial.

Outcome measures will be both use of appropriate restraints for the age of the child, and incorrect use of restraints, and will be collected 2 months after the intervention has been implemented using a proven observational method [21]. Masked observers will attend each site over a 1-2 hour period during morning drop-off times. Potential participants will be approached as they pull into a parking spot outside the institution, and informed consent will be gained from all participating parents. Initial observations will be made with the child in situ. The driver of the vehicle will then be invited to participate in a brief interview. All refusals will be recorded and brief observational and demographic data collected to allow evaluation of potential bias between participants and non-participants. A brief structured interview will be conducted with those consenting to record parent/guardian age, gender, education, and information about age and gender of child, usual child restraint use, number and age of children in family. A detailed examination of the restraint installation by trained observers will be conducted while the interview is taking place.

Although it would be ideal to measure outcome after a longer time period, it is difficult in practice to follow-up children over two calendar years. Most of the children aged 4-5 at the beginning of the intervention year will move to primary (elementary) school the following year. It would not be practical to collect follow-up data from children at this time as they will move to a range of different schools and direct observation will not be feasible. While 6 month follow-up data could be collected by phone, likely differential reporting bias would mean that such outcome data would be severely compromised.

In order to assess compliance and uptake of the program, records will be kept of which families attend the education sessions, and receive individualised fitting services or subsidised child restraints. Information about alternative road safety or restraint programs administered by either intervention or the control sites will be collected. Importantly, as understanding practical issues about how to implement such programs is vital to further roll-out of successful programs, process measures will also be evaluated by asking the director and staff of the intervention group centres to complete a short questionnaire about the implementation of the program.

Research assistants conducting the pre-and post-trial observations will be blinded to the intervention/control status of each centre. Furthermore, research staff will be trained appropriately and outcome measurements will be based on standardised objective criteria, minimizing opportunities for measurement error. As pre-trial observations are collected by self-administered questionnaires, research staff will not observe children until after the intervention has been implemented. For both intervention and control centres, research staff conducting post-trial observations will present parents or guardians of children with written information about appropriate use of child restraints and offer advice if any child is observed in inappropriate restraints or using restraints incorrectly. Appropriate bilingual staff will be employed to conduct baseline interviews, implement the program and conduct post-trial observations, to meet the language needs of participating families.

On 1 March 2010 new national child restraint laws were enacted in NSW, mandating appropriate restraint use by children up to age 7. Enforcement of these laws was delayed until 30 June 2010 to allow parents and carers time to fully understand and comply with the new laws. The new laws will impact on all pre-school centres and parents in the trial. The impact of the new laws is that the baseline rate of appropriate child restraint use may increase in all centres, whether control or intervention. It is unlikely that the rate of incorrect use will change as the social marketing and education campaigns behind the new laws are focused more on use of appropriate restraints rather than on reducing incorrect use. Baseline interviews will be conducted before the enforcement of the new law at all centres, and for most centres before the 1 March introduction.

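### The installation check runs during the driver interview, so a chance remark could unmask the examiner before that part of incorrect use is scored

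*Protocol article*

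**What the plan says.** All of this is in the protocol article, Methods, Intervention, unless another section is named.

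- **Outcomes.** "Outcome measures will be both use of appropriate restraints for the age of the child, and incorrect use of restraints". Both enter the primary analysis (Sample size and statistical analysis).
- **Setting.** "Masked observers will attend each site over a 1-2 hour period during morning drop-off times", and "Potential participants will be approached as they pull into a parking spot outside the institution".
- **Order of steps.** "Initial observations will be made with the child in situ". "The driver of the vehicle will then be invited to participate in a brief interview". Then: "A detailed examination of the restraint installation by trained observers will be conducted while the interview is taking place".
- **Interview content.** Demographic items, family size and the child's usual restraint use. No question about the program is listed.
- **What only the intervention arm is to receive.** All families get the DVD, brochures and a free voucher for a fitting station, and a restraint is available for AUD 50 to those who need one. For the centres: "Centres will be asked to display restraint information provided in prominent positions".
- **Safeguards.** "Research assistants conducting the pre-and post-trial observations will be blinded to the intervention/control status of each centre". Staff are trained and the criteria are standardised and objective.

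**The concern.** Masking at the outset means that the observer arrives without knowing the arm. It does not stop the observer from learning it on site. The stated order puts the installation examination alongside a conversation about restraints with a driver who knows what the family has been given. A mention of the DVD, the voucher or the subsidised seat would point to the intervention arm, and control drivers have none of these to mention.

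Allocation is by centre and a visit lasts one to two hours, so one remark can carry over to every later car that morning, including the first-step observations of those cars. An examiner who knows the arm might judge a borderline fitting more leniently. The Background counts belt tension and attachment to the vehicle among the forms of incorrect use, and both may involve some judgement. At stake is the assessor-blinded claim made in the Abstract and the Discussion, for one of the two primary outcomes.

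**Working it through.** **1. Which part of the outcome is exposed.** For a given car, errors visible with the child seated are observed before the interview. The installation examination overlaps it. So only the installation component is exposed by that car's own interview. For later cars at the same centre, both steps would follow the disclosure.

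**2. How often a remark would have to occur.** Illustration, with assumptions not in the documents: 20 cars per centre, one team, examiner within earshot, each driver mentioning the program with probability p. The expected share of cars examined at or after the first remark is (1/20) × Σ[1 − (1 − p)^k], k = 1 to 20.

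- p = 5%: 39%
- p = 7%: 49%
- p = 10%: 60%

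Under these assumptions, occasional remarks are enough to unmask about half the cars.

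**3. The plan's own size, as a check on the inputs.** Sample size and statistical analysis gives an intra-class correlation of 0.06, 20 children per centre, and 20 centres rising to 28.

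- Design effect: 1 + 19 × 0.06 = 2.14.
- 60% against 80%, two-sided 5%, 80% power, continuity correction: 91 per arm. 91 × 2.14 = 194.7; divided by 20 this is 9.74, so 10 centres per arm. This reproduces the stated 20.
- Incorrect use 60% against 40%: power is 78.5% with 10 centres per arm and 90.4% with 14, in keeping with the stated 80%.

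None of these figures depends on the present point.

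**4. Possible size of the bias.** Bias = share of intervention cars unmasked × share of incorrect uses then passed × incorrect use open to re-judgement. The 60% incorrect use is from the plan. The 50% unmasked and the 10-20% passed are assumptions.

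- All incorrect use open: 0.50 × 0.10 × 0.60 = 3 points; at 15%, 4.5 points; at 20%, 6 points.
- Half the errors already fixed in the first observation (assumption), and an error at either step counting as incorrect: 0.50 × 0.10 × 0.30 = 1.5 points; at 15%, 2.25 points; at 20%, 3 points.

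The bias scales with the unmasked share and is zero if the examiner never hears the interview.

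**5. Effect on the false-positive rate, with no true effect.** SE = √(2 × 0.6 × 0.4 × 2.14 / n): 0.0717 for n = 200 per arm (20 centres) and 0.0606 for n = 280 (28 centres). Rejection probability = Φ(d/SE − 1.96) + Φ(−d/SE − 1.96).

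| Bias d | 20 centres | 28 centres |
|---|---|---|
| 1.5 points | 5.5% | 5.7% |
| 2.25 points | 6.1% | 6.6% |
| 3 points | 7.0% | 7.9% |
| 4.5 points | 9.6% | 11.5% |
| 6 points | 13.3% | 16.8% |

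**The case against.** The protocol states masking twice and adds training and standardised objective criteria. The child is observed in place before the interview starts. The interview has no program question, so disclosure would be incidental. Examining and interviewing at the same time is compatible with two different people standing apart, and a condensed article may leave such detail to the observation manual. The new restraint laws and their campaigns reach every family, so talk of a new seat need not identify the arm.

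Most of this stands, and it rules out several stronger readings.

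- *A reader might infer that incorrect use as a whole is scored during the interview.* It is not; the first observation precedes it for each car. An error already scored there cannot be undone by a lenient installation check.
- *A reader might infer that the displays give the allocation away.* Observers work at parking spots outside the centre, and nothing says that the displays can be seen from there. The standard program also sends posters to all registered services.
- *A reader might infer that unmasking will happen, only in one arm, and will favour the intervention.* The one-sided materials make that plausible, but disclosure, leniency and direction are all inferences.
- *A reader might infer that the same staff deliver the program and assess it,* because bilingual staff are mentioned for both tasks in one sentence. The text does not say that they are the same people.

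What the objection does not remove is the stated overlap. No separation of examiner from interview is described, and starting out masked does not prevent carry-over within a centre.

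**Conclusion.** The point holds as a risk to the assessor-blinded claim that is cheap to reduce. It is not a contradiction in the protocol and not evidence that assessment will be biased. The exposed part is the installation component of incorrect use, plus any later assessments at a centre whose allocation has been revealed.

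The documents do not allow its size to be derived. With 50% of intervention cars unmasked and 10-20% of incorrect uses then passed, the false benefit is at most 3-6 points against the 20-point target, and about half that if half the errors are already fixed in the first observation. The halved figure takes the first-step scores as unaffected, which may not hold for later cars at an unmasked centre. The planned sample size is untouched.

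**What to change.** 1. When drivers are approached, ask them in both arms not to mention any program they have received.
2. Conduct the interview out of the examiner's earshot, or hold back the restraint questions, until the first-observation and installation scores for that car are closed. Distance is better than reordering alone, because a remark made after one car is closed can still carry over to the next.
3. Record for each centre and car whether and when the allocation was revealed, and report the frequency of unmasking by arm.
4. As a sensitivity analysis, compare incorrect use on the items from the first observation alone. Read it beside the timing record, since for later cars at an unmasked centre these items also follow the disclosure. Do not exclude unmasked cars: that is a post-randomisation exclusion falling mostly on one arm, and probably on the families most engaged with the program.

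There is no need to cover displays, since nothing shows that they can be seen from the parking area.

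**Cost.** A few lines in the observation procedure and extra fields on the form. If distance cannot separate the two tasks, each car takes a little longer. With 20 cars in 60 to 120 minutes, one team and one visit (assumed), there are 3 to 6 minutes per car, so separation by distance is preferable to delay.

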### Sample size and statistical analysis

This study has 80% power to detect a 20% increase in use of appropriate child restraints from 60% to 80%, as significant at the 5% level. Previous research has indicated that educational and incentive based interventions may increase use of restraints by about 20% [25]. In NSW the use of appropriate child restraints in 20 centres in Sydney varied from 30-70% [31]. However, among centres from local government areas with low educational attainment, the average use of appropriate child restraint use is 30-40%. If the effect of the implemented RTA general marketing program raises the base rate in controls to 60%, the study will be adequately powered to find an effect of a 20% increase. However, it will also have power to detect a 20% effect if the base rate of restraint use remains between 30-50%. Increasing the rate to 80% is feasible: the base rate of child restraint use in centres in areas with high education and high socioeconomic status is around 70%, so this increase is possible. Previous work has allowed estimation of the intra-class correlation as 0.06, based on proportion using appropriate restraint at 9 centres [31]. Allowing for a minimum of 20 eligible children at each centre (with an average number of slightly more than 20 anticipated) would require 20 centres. Further allowing for 30% centre drop-outs through the course of the study requires 14 intervention centres and 14 control sites. This sample size will also allow 80% power to establish whether incorrect use of restraint systems can be reduced from 60% of children using restraints to 40%. Direct observation of children in pre-school settings in Sydney found that 65% of children using forward facing child restraints and 60% of children in booster seats were incorrectly using the restraints [31].

Data will be analysed on an intention-to-treat basis. The primary analysis will compare the proportion of each of the two outcome measures (appropriateness and correctness of restraint use) at each centre between the intervention and control groups using Donner's adjusted chi-square test[32]. Logistic regression modelling will be used to explore predictors of each outcome measure, using generalised estimating equations (GEE) to allow for clustering of data by centre.

The study protocol was approved by the Human Research Ethics Committees of the University of Sydney and the University of NSW.

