Restricted randomisation will be conducted using the unique identifiers and summary data from the baseline survey to ensure adequate balance of important factors. The five balance criteria will be (i) service type exactly balanced between groups; (ii) self-reported restraint choice for the 3-5 year-old children attending the service (proportion appropriately restrained): mean proportions in each group differ by no more than 5% in relative terms (i.e. ratio of means between 0.95 and 1.05); (iii) mean proportion of families with annual household income below AU$60,000 in each group differ by no more than 10% relatively; (iv) mean proportion of families who speak a language other than English at home in each group differ by no more than 10% relatively; and (v) mean size (number of children aged 3-5 years enrolled) of centres in each group differ by no more than 10% relatively. The randomisation process will be fully concealed as the statistician will allocate the centres at a site remote to the recruitment site and will only have access to a list of centres recruited. Of the 28 centres in the study, 14 centres will be randomly allocated to each of the intervention and control groups.

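### The primary test takes no account of the factors that restrict the randomisation, so its true size depends on an unstated prognostic strength; the effect is modest

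*Protocol article*

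**What the plan says.** Methods describes the allocation: "Restricted randomisation will be conducted using the unique identifiers and summary data from the baseline survey to ensure adequate balance of important factors". There are five criteria. Service type is balanced exactly. The ratio of the arms' mean baseline appropriate-use proportions must lie between 0.95 and 1.05. Low income, home language and centre size must each agree within 10% relatively.

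Under Sample size and statistical analysis, the primary analysis compares each of the two outcomes "at each centre between the intervention and control groups using Donner's adjusted chi-square test". The only model mentioned is a logistic GEE. Its purpose is to explore predictors, it allows for clustering, and it is not tied to the restriction factors. No permutation test is mentioned.

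The same section assumes centre losses: "Further allowing for 30% centre drop-outs through the course of the study requires 14 intervention centres and 14 control sites".

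The baseline survey (Methods) records restraint type, frequency of use and seating position. It lists no measure of incorrect use.

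**The concern.** Restricted randomisation rules out allocations that are unbalanced on the chosen factors. If those factors predict outcome, the arm difference varies less than it would under free allocation. A test that does not know this uses too large a variance and becomes conservative.

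A second effect works the other way. Donner's test refers its statistic to chi-square with 1 df, as if the estimated intra-class correlation were known. With 20–28 centres that makes it slightly liberal.

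Which effect prevails depends on a quantity that the article does not give. At stake are the calibration of the primary p-value and some power, since the centre baseline proportion is already collected but unused in the primary test. The article names a specific test, so this is a fixed choice and not a detail left to a fuller document.

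**Working it through.** **Inputs from the article.** Testing is "as significant at the 5% level" (taken as two-sided; the article does not say). Appropriate use rises from 60% to 80%, and incorrect use falls from 60% to 40%. For the ICC: "Previous work has allowed estimation of the intra-class correlation as 0.06". For cluster size: "Allowing for a minimum of 20 eligible children at each centre". There are 20 centres before the drop-out allowance and 28 after it.

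**The plan's own figure.** The design effect is 1 + (20 − 1) × 0.06 = 2.14. For 60% against 80% at 80% power, the two-proportion formula gives 82 per arm, or 91 with continuity correction. Then 91 × 2.14 / 20 = 9.74, so 10 per arm and 20 centres, as stated. Next, 20 / 0.7 = 28.6, against 28 stated. By formula, 10 per arm gives 85.3% power for 60% against 80%, and 78.5% for 60% against 40%. With 14 per arm the figures are 94.6% and 90.4%. The sample size is not in dispute.

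**The test.** With equal clusters of m children, Donner's statistic is the sum over arms of M(P_arm − P)² / [C × P(1 − P)]. Here M is the number of children in the arm and C = 1 + (m − 1) × estimated ICC. No restriction factor enters.

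**Small-sample effect alone.** The between-centre variance is estimated on 28 − 2 = 26 df, or 20 − 2 = 18 df. As an approximation, using the limit 1.96 where a t limit is due gives P(|t26| > 1.96) = 6.1% and P(|t18| > 1.96) = 6.6%.

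**Simulation.** All five criteria were applied, with 20 children per centre and an outcome ICC of 0.06. There were 8,000 null runs per setting, so the Monte Carlo standard error near 5% is √(0.05 × 0.95 / 8000) = 0.24 points. Assumptions not in the article: baseline mean 45%, 20 baseline respondents per centre, service types split evenly and not prognostic, and income and language correlated 0 or 0.3 with outcome. The correlation in the tables is between a centre's latent baseline and outcome levels. The adjusted analysis is a centre-level regression on arm, service type and baseline proportion, with a t reference. Each cell of the first table gives results for income/language correlation 0, then 0.3.

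| Correlation | Donner size, 28 centres | Adjusted size, 28 centres | Donner size, 20 centres | Adjusted size, 20 centres |
|---|---|---|---|---|
| 0 | 6.2%, 5.2% | 5.2%, 4.3% | 6.8%, 5.2% | 5.4%, 4.1% |
| 0.5 | 5.4%, 4.3% | 5.0%, 4.2% | 4.9%, 4.7% | 4.4%, 4.3% |
| 0.7 | 4.0%, 3.7% | 5.0%, 4.2% | 4.2%, 3.9% | 4.8%, 4.2% |
| 0.9 | 3.7%, 2.6% | 5.6%, 4.4% | 3.1%, 3.0% | 4.7%, 4.3% |

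**Restriction isolated** (correlation 0.5, income and language 0.3). With 28 centres, Donner's size is 5.8% when allocation is restricted only by service type and 4.3% under all five criteria. The SD of the arm difference falls from 0.0602 to 0.0564, so the variance falls by 1 − (0.0564/0.0602)² = 12%. With 20 centres the size goes from 7.1% to 4.7%.

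**Power for 60% against 80%** (4,000 runs, income and language 0.3):

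| Correlation | Donner, 20 centres | Adjusted, 20 centres | Donner, 28 centres | Adjusted, 28 centres |
|---|---|---|---|---|
| 0 | 86.0% | 81.9% | 95.0% | 93.8% |
| 0.5 | 86.7% | 85.1% | 95.7% | 95.3% |
| 0.9 | 88.1% | 91.1% | 96.2% | 97.8% |

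**Narrower restriction.** Simulations restricted only on service type and the 5% baseline ratio agree. Donner's size was 5.7–6.5% with no prognostic value, 4.9–5.5% at correlation 0.5, 4.1–4.7% at 0.7 and 3.0% at 0.9. If the two factors explain 50–70% of between-centre variance, power for the 20-point effect with 10 per arm was 81% for Donner's test and 82–85% adjusted. For a 15-point effect with 14 per arm it was 70–71% against 74–79%.

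**The case against.** The strongest reply is that Donner's test is an established method for cluster trials and that, where the restriction matters most, it errs on the safe side. At moderate prognostic strength the two effects roughly cancel and size is near 5%. That stands.

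The strongly prognostic cases are also near a ceiling. A centre proportion from 20 respondents at ICC 0.06 has reliability 20 × 0.06 / 2.14 = 0.56, so even a perfectly stable centre rate would leave the baseline explaining only 56% of between-centre variance. Forty respondents would give 40 × 0.06 / 3.34 = 0.72. The article itself regards self-report as less accurate than observation, and it expects a new restraint law to shift appropriate use around the time of the baseline survey. Both weaken the link. This limits the likely power gain but does not remove the mismatch between design and test.

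A reader might infer three stronger things, none of which the article supports:

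- **That the primary p-value is prone to false positives.** Only the case without prognostic value is liberal, by about 1–2 points.
- **That a baseline rate is discarded for both outcomes.** None is listed for incorrect use. Adjusting that outcome for an unrelated baseline would cost power: in one run for 60% to 40% with 10 per arm, 75.9% for Donner's test (partly owing to its liberal size) against 70.5% adjusted.
- **That centre losses will undo the balance.** The 30% is a sample-size allowance. Balance is not guaranteed after losses, but no imbalance has been quantified, and the 20-centre runs applied the restriction to 20 centres without modelling loss from 28. This argument is secondary.

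**Conclusion.** The point holds in a limited form. The primary test ignores all five restriction factors and the baseline appropriate-use proportion. Its true size is about 5.7–6.5% if the factors are not prognostic (6.8% in one 20-centre setting), close to 5% at moderate strength, and about 3–4% if they are strongly prognostic (2.6% at the extreme). The adjusted centre-level analysis stays within about 4–5.6% throughout.

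Power for appropriate use is not in doubt: with 20 centres Donner's test exceeds 80% at the planned effect in every setting run. Near-nominal size at moderate strength comes from two offsetting errors, and nobody can confirm in advance that they offset. All of this rests on the assumed prognostic strength and the simulation settings listed above. The change is worth making because it is cheap, not because the planned result would be unsound.

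**What to change.** - **Appropriate use:** make the primary analysis a linear regression of the centre proportion on arm, service type and centre baseline appropriate-use proportion. Use a t reference with df = centres minus parameters (28 − 4 = 24, or 20 − 4 = 16 if 20 centres remain). Report the adjusted risk difference with its 95% CI.
- **Incorrect use:** use the same approach, adjusting for service type only (28 − 3 = 25 df, or 20 − 3 = 17).
- **Alternative:** a permutation test over the allowed allocations, which respects all five criteria. In the simulation about 5.5% of allocations balanced by service type were acceptable with 28 centres. With 14 centres of each type (assumed) that is about 3,432² × 0.055 ≈ 648,000, which is ample.
- **Keep** Donner's test as a supporting analysis.

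**Cost.** Only the wording of the analysis section changes, before unblinding, and no new data are needed. If the factors are not prognostic, nominal power falls up to about 4 points below Donner's at the planned effect, and about 6 points at a 15-point effect, partly because Donner's size is then inflated. The regression covers two of the five factors. When income and language also matter it is slightly conservative (4.1–4.4% in the runs above).

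### With 20 to 28 centres, Donner's adjusted chi-square on its usual reference, applied after restricted randomisation, does not assure the stated 5% level in either direction

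*Protocol article*

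**What the plan says.** All but the allocation comes from the protocol article, section Sample size and statistical analysis.

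- **Test.** Each of the two outcomes is compared "between the intervention and control groups using Donner's adjusted chi-square test[32"]. The sizing paragraph treats a difference "as significant at the 5% level". No critical value, degrees of freedom or small-sample rule is given.
- **Size.** The main target is an "increase in use of appropriate child restraints from 60% to 80" per cent with 80% power. With 20 children per centre this "would require 20 centres", raised to 28 for 30% centre drop-out. The same size is said to give 80% power to show that "incorrect use of restraint systems can be reduced from 60% of children using restraints to 40" per cent.
- **Clustering.** "Previous work has allowed estimation of the intra-class correlation as 0.06, based on proportion using appropriate restraint at 9 centres". No value is given for incorrect use.
- **Allocation (Methods).** "Of the 28 centres in the study, 14 centres will be randomly allocated to each of the intervention and control groups". Allocation is restricted on service type, baseline self-reported appropriate use (within 5% relative), and income, home language and centre size (each within 10% relative). The primary test uses none of these factors.

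**The concern.** Donner's statistic divides the Pearson chi-square by an inflation factor estimated from the scatter between centres. Read against chi-square on 1 degree of freedom, it makes no allowance for error in that estimate. With few centres this makes rejection too easy.

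The restricted allocation pulls the other way. It removes chance imbalance between the arms, but an unadjusted variance still counts that imbalance as noise. The two effects have different causes and need not cancel. At stake are the error rate behind both primary conclusions, and power figures that depend on the critical value.

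**Working it through.** **Inputs.** Two-sided 5% (a 1-df chi-square test is two-sided), power 80%, rates 60% vs 80% and 60% vs 40%, intra-class correlation 0.06, m = 20 children per centre, K = 20 or 28 centres. All are from the sample size section.

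**1. The plan's own figure.**
- Design effect: 1 + (20 − 1) × 0.06 = 2.14.
- Two-proportion size for 60% vs 80% with continuity correction: 91 per arm. 91 × 2.14 = 194.7 and 194.7/20 = 9.74, so 10 centres per arm and 20 in all. This reproduces the plan. Without the correction: 82 × 2.14/20 = 8.77, so 9 per arm.
- Drop-out: 20/0.7 = 28.6, against 28 stated.
- For 60% vs 40% with 10 centres per arm, the normal approximation gives 78.5%, close to the stated 80%.

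**2. Level if the balance factors do not predict outcome.** With equal centre sizes the statistic is

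X² = Σ M(pᵢ − p)² / {[1 + (m − 1)r] p(1 − p)},

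where M is the number of children per arm and r = (MSC − MSE)/(MSC + (m − 1)MSE). MSC, the between-centre mean square, has K − 2 degrees of freedom, so X² behaves approximately as the square of a t variable on K − 2.
- Analytic: P(|t| > 1.96) = 6.6% on 18 df and 6.1% on 26 df.
- Beta-binomial simulation at the plan's inputs: about 6.2–6.6% with 20 centres and 5.9–6.1% with 28.
- The same statistic referred to F(1, K − 2): about 4.7–5.1%.

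**3. Level under the restriction.** If the balance factors explain a share R² of the variance of the observed centre proportions and balance is perfect, the level is about P(|t| > 1.96/√(1 − R²)). At R² = 0.10 this is 5.4% (20 centres) and 4.9% (28). At R² = 0.25 it is 3.6% and 3.2%.

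Simulation with the protocol's limits on baseline use, income, language and size gave the levels below. Service type was not simulated. Assumed: baseline use 35%, 20 baseline replies per centre, and the spread of the covariates.

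| Observed baseline–outcome correlation between centres | Chi-square, 28 / 20 centres | F(1, K−2), 28 / 20 centres |
|---|---|---|
| 0 | 6.1% / 6.5% | 5.0% / 5.0% |
| 0.17 | 5.7% / 6.2% | 4.7% / 4.7% |
| 0.28 | 5.2% / 5.9% | 4.2% / 4.5% |
| 0.28, income and language modestly predictive | 4.8% / 5.4% | 3.9% / 4.0% |
| 0.39, income and language modestly predictive | 3.9% / 4.9% | 3.1% / 3.6% |
| 0.44, income and language more predictive | 3.4% / 4.4% | 2.7% / 3.2% |

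**4. Unadjusted power at 20 centres, chi-square against F(1, 18), simulated.**
- 60% to 80%: about 85% against 81–82%.
- 60% to 40%: about 78–79% against 74%.
- 30% to 50%: about 79–80% against 75–76%.
- 40% to 60%: about 78% against 74%.

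With all 28 centres and F(1, 26), power is about 88–93%.

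**The case against.** **The reference distribution is not stated.** The article condenses a fuller plan, and an analysis plan that is not shown may set a t or F critical value. That stands, so the figures are conditional on the usual reference. But the article does name a specific test and level, and the ordinary reading of that name is chi-square on 1 df.

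**A reader might infer that the true level is simply 6–7% for each outcome, so that both are declared significant too easily.** The documents do not support this. At the stated inputs the level without any offset is at most about 6.6%; reaching 7% needs smaller or more unequal centres or a larger correlation than the plan gives. More important, the trial's own allocation can push the level below 5%. The Background cites income, education and non-English-speaking background as risk factors, and the baseline measure concerns the same behaviour as the first outcome.

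**Nor can it be said that the restriction does nothing for incorrect use.** No measure of incorrect use is balanced, but the Background links incorrect booster use to low socioeconomic and non-English-speaking families, and income and home language are balanced. Its intra-class correlation is also unknown: at 0.02, with negative estimates set to zero, the level is about 5.6%.

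**The offset is not assured either.** Baseline is a questionnaire completed before the new law was enforced, and the outcome is direct observation afterwards, which could weaken the correlation. An offset of unknown size is no substitute for a calibrated test.

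**Conclusion.** The point holds in a limited form. On its usual reference the named test has a level of about 6.3–6.6% with 20 centres or 5.9–6.1% with 28 when the balance factors are unrelated to outcome. It falls towards or below 5% as they become predictive. Roughly 3.5–6.5% covers the assumptions tried. That range rests on assumed correlations and is not a bound. The incorrect-use figure also assumes an intra-class correlation of 0.06.

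The 80% power claim for 60% to 80% survives a small-sample reference at 20 centres. The claim for incorrect use does not: about 74%, of which roughly 4 points are due to the reference. With all 28 centres retained, power is not a concern. The departure is small, but it affects both primary outcomes and is easily corrected before analysis.

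**What to change.** In the section Sample size and statistical analysis, replace the chi-square(1) reference with one of these, named in advance:

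1. **Preferred.** Either a centre-level analysis adjusted for the balance factors, with a t reference on centres minus estimated parameters, or a permutation test over the allocations that met the balance criteria. Adjusting for all five factors uses 7 parameters (intercept, arm, five factors), leaving 20 − 7 = 13 or 28 − 7 = 21 degrees of freedom. The permutation test requires the set of acceptable allocations to be kept.
2. **Minimum.** Keep the unadjusted statistic and refer it to F(1, K − 2), K being the number of centres analysed. State that this is conservative if the balance factors predict outcome (2.7–4.5% at observed correlations of 0.28 or more in the table).

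Restate unadjusted power at 20 centres on the F basis: about 82% for 60% to 80%, 74–76% for a 20-point rise from 30–40%, and 74% for incorrect use. Add the 28-centre figures (88–93%), and say that 0.06 is assumed for incorrect use.

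**Cost.** A sentence or two of analysis wording and revised power figures. Nominal power falls by 3–4 points at 20 centres and 1–2 at 28. Adjustment recovers part of this if the factors predict outcome.
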